**Fig. 3 Fig3:**
[figure not shown]
Schedule of cohorts. Detailed legend: Not applicable

**Fig. 4 Fig4:**
[figure not shown]
CONSORT flowchart showing participant pathway through the trial. Detailed legend: Not applicable

### Assessment

#### Primary outcome and measure

The primary outcome is carers’ mental wellbeing at 20 weeks assessed using Warwick Edinburgh Mental Wellbeing Scale (WEMWBS [29]). WEMWBS is a self-report measure comprising 14 short statements focusing on positive wellbeing. Each statement is rated on a 5-point Likert scale, resulting in the possible scores range from 14 to 70 (higher score indicates better mental wellbeing). Since its validation, WEMWBS has been widely used in epidemiological studies, including the Health Surveys in England and Scotland [11, 31, 32]. It has been established that an increase of 3 points in WEMWBS is a meaningful change post intervention, based on a wide range of mental health intervention trials undertaken in different populations [13, 33].

#### Secondary outcomes and measures

A range of secondary outcomes will be considered, including changes in the following:

Carers’ mental health knowledge, measured using the Mental Health Knowledge Schedule (MAKS [34]). MAKS has two sections: the former to investigate participants’ knowledge of mental health; the latter for contextualising the responses. Possible scores range from 6 to 30 by summing up the scores of the first section of six items. Higher scores of MAKS indicate better level of mental health knowledge.

Carers’ appraisal of caregiving experience, assessed using the Experience of Caregiving Inventory (ECI [8]). There are 66 brief statements each requiring a rating on a 5-point ordinal scale (from 0 = never to 4 = nearly always) in the ECI. These are categorized into ten subscales; eight negative subscales summing into the total negative appraisal total (possible scores range from 0 to 208; higher scores indicate poorer outcome), and two positive subscales totaling into the positive appraisal score (possible scores range from 0 to 56; higher the scores better the positive perspective).

Carers’ wellbeing and perceived support, measured with the Carers’ Wellbeing and Support Questionnaire (CWS [35]). CWS contains two subscales: wellbeing (higher scores indicate better wellbeing) and perceived support (higher scores indicated lower satisfaction).

Criticism and emotional over-involvement in the family, assessed by Family Questionnaire (FQ [36]). FQ comprises 20 short questions, with 10 of these covering the criticism subscale, and the remainders the emotional over-involvement subscale. Higher scores indicate poorer outcomes on both subscales.

Carers’ quality of life assessed using Euro-QoL 5-level (EQ-5D-5L [37]). EQ-5D-5L comprises two components: health state description covering the domains of mobility, self-care, usual activity, pain/discomfort and anxiety/depression; and an overall evaluation using a visual analogue score (EQ-VAS). The EQ-VAS asks the participants to rate their subjective rating of health ranging from 0 to 100, where 100 implies the best health one can imagine, and 0 the worst.

#### Service use

In addition to these measures, service use information by the participants will be collected to describe usual care.

#### Process evaluation outcomes and data

The trial has an inbuilt process evaluation study to explore participants’ usage patterns and subjective experience of participants in using COPe-support. In order to understand when and how participants access and use the online intervention, we will collect usage data which the intervention and control platform automatically monitors and records. These include:
Number of log-ins on separate days per participant (both arms)Average page views per log-in per participant (both arms)Total time spent on the platform per participant (both arms)Average time spent per page view on the platform per participants (both arms)Total number of posts per participant made to the peer-to-peer forum (intervention arm only)Total number of posts per participant made to the Ask the Experts forum (intervention arm only)

Perceived acceptability will be determined through interviewing a purposive sample of 20% of the participants in the intervention arms of the trial after all the data collection procedures (i.e. about 36 out of the 180, or less should data saturation, that is no further data is being collected that adds to the content of existing themes, be reached in the iterative analysis process [38]). For the individual interview, purposive sampling will be used to identify participants to ensure representation of diverse experiences and views from those with ethnic minority backgrounds, different caregiving experiences and roles, and usage patterns. The interview is designed to be semi-structured and conducted over phone or Skype, suiting the participants’ preference and convenience.

### Data collection

Assessments will be completed online at baseline (i.e. no more than two weeks prior to randomization and allocation), half-way through the intervention use (10-week), post intervention (20-weeks), and 40-week follow-up. All outcome measures are self-completed questionnaires as described above. At each time point, we will invite the participants to undertake an online assessment through our secure platform. At study enrolment, we will also collect data on participant’s demographic and caregivng-related information (e.g. the gender of the cared-for person, are they living together or separately, and how much time they spend on caring for their loved one in the previous week). At each assessment time point, participants will receive up to six email-reminders over a four-week window, linking them to an online platform through which they can complete the assessment.

We will collect the usage data during the intervention time (20 weeks) following completion of all outcome data collection, i.e. at the end of 40 weeks. These data will be collected from our intervention (and control) platform which automatically record individuals’ usage.

On completion of each assessment, participants will be emailed an Amazon voucher to thank for their time and participation (i.e. £10 for the first, £5 for the second and third respectively, and £10 for the fourth and last). We will offer an additional £10 Amazon voucher for those who give an interview. Figure 5 shows all the measures used and data collection schedule.

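### The 20-week reminders all lead to one long assessment; a WEMWBS-only option in the last reminders would be a cheap way to protect the primary outcome

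*Protocol article*

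**What the plan says.** The Data collection section has every outcome self-completed online at baseline, 10, 20 and 40 weeks. At each point, "participants will receive up to six email-reminders over a four-week window, linking them to an online platform through which they can complete the assessment". A voucher follows completion of each assessment; the third, at 20 weeks, earns £5. No other contact route for a non-responder is described.

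The primary outcome is short: "WEMWBS is a self-report measure comprising 14 short statements" (Primary outcome and measure). The secondary battery is long. For the ECI, "There are 66 brief statements each requiring a rating on a 5-point ordinal scale"; "FQ comprises 20 short questions"; MAKS is scored "by summing up the scores of the first section of six items" and has a second, contextual section of unstated length. EQ-5D-5L has five domains and a visual analogue score. "CWS contains two subscales", with no item count given. Service use is collected as well.

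The Sample size section needs 143 carers per arm and recruits 360 to allow for 20% attrition. The Statistical analysis plan section includes everyone with at least one post-randomisation measure, whatever their usage or withdrawal status. It relies on missing-at-random without imputation and adds a sensitivity analysis that sets missing values to the highest and lowest observed.

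**The concern.** As described, the procedure asks the same thing of a disengaging carer up to six times: open the assessment and finish it. The primary outcome is a small part of that request and gets no priority. A carer who would answer 14 questions about their own wellbeing, but not a long caregiving inventory, is given no way to do so.

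These carers matter to the intention-to-treat answer. The article expects attrition and disengagement (Discussion) and notes that online trials can have poorer retention (Background). Missing-at-random is least secure among people who have stopped engaging, so an observed 20-week WEMWBS is worth more there than one supplied by the model. The sample size also has almost no margin beyond the planned loss.

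**Working it through.** **1. Item burden** (counts from the two outcome sections)

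- WEMWBS 14
- MAKS 6 (scored section only)
- ECI 66
- FQ 20
- EQ-5D-5L 5 + 1 = 6

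The secondary items with a stated count sum to 6 + 66 + 20 + 6 = 98. The total is 14 + 98 = 112, and the WEMWBS share is 14/112 = 12.5%. CWS, the second MAKS section and service use come on top, so for the full battery 12.5% is an upper limit.

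The content of the 20-week assessment is set out in Fig. 5, which was not available in the copy read. The text hypothesises knowledge, appraisal, support and quality of life at all follow-ups, but does not list the FQ there. Without the FQ the counted total is 92 and the share 14/92 = 15.2%, still before CWS. The conclusion does not change.

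**2. The plan's own sample size**

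Inputs: difference 3, SD 9, 80% power, 5% significance (two-sided assumed), 1:1 allocation.

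n per arm = 2 × (1.960 + 0.842)² × 9² / 3² ≈ 141.3, so 142. The exact t-based version gives 143, as stated. Inflation: 286 / 0.80 = 357.5, so 358, rounded to 360; 360 − 286 = 74, as stated. The sample size is not in error.

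**3. Margin**

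180 × 0.80 = 144 per arm at the planned loss, one more than the 143 needed.

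Power = Φ(3 / (9 × √(2/n)) − 1.96), with n = 180 × (1 − loss). At n = 144 this is Φ(2.828 − 1.960) = 80.7%.

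| 20-week loss | n per arm | Power |
|---|---|---|
| 10% | 162 | 85.1% |
| 15% | 153 | 83.0% |
| 20% | 144 | 80.7% |
| 25% | 135 | 78.2% |
| 30% | 126 | 75.4% |
| 40% | 108 | 68.8% |

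**4. What a short form could recover**

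The article gives no recovery rate, so 10% and 25% of non-completers are assumptions. At 20% loss, 360 × 0.20 = 72 carers lack 20-week data. Recovering 10–25% gives 7 to 18 more primary outcomes, and retention rises from 288/360 = 80% to about 82–85%.

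| Loss before short form | No short form | 10% recovered | 25% recovered |
|---|---|---|---|
| 20% | 80.7% | 81.7% (n = 147.6) | 83.0% (n = 153) |
| 30% | 75.4% | 77.1% (n = 131.4) | 79.5% (n = 139.5) |
| 40% | 68.8% | 71.6% (n = 115.2) | 75.4% (n = 126) |

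At 20% loss the standard error falls by a factor of √(144/147.6) = 0.988 to √(144/153) = 0.970, that is by 1–3%.

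These figures ignore baseline adjustment and repeated measures. The planned mixed model should do better than the simple calculation, and a recovered 20-week value adds less for a carer who already has week-10 or week-40 data.

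**5. The highest/lowest sensitivity analysis**

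The gap between an arm's two imputed means is the missing fraction times the observed range. If that range reached the scale limits (70 − 14 = 56, an upper bound), 20% missing gives 0.20 × 56 = 11.2 points. After 10–25% recovery it is 0.18 × 56 = 10.1 to 0.15 × 56 = 8.4 points.

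**The case against.** A reader might infer that a carer who stops part-way loses the WEMWBS, or must complete everything or return nothing. The article does not support that. It does not say that the battery is all-or-nothing, that WEMWBS comes late, or that partial answers are discarded. Question order and partial saving are matters an article commonly leaves to the full protocol, and may already be handled well. This objection stands, and nothing here rests on the contrary.

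The retention evidence is also better than the concern suggests. The internal pilot required at least 80% retained at 20 weeks and is reported as having met all its criteria under the trial's own procedures. The actual rate is not given, so the margin may be larger than one carer per arm. Vouchers, weekly updates in both arms, later access to COPe-support for controls and a facilitation protocol all support retention. Missing week 20 does not remove a carer who supplied week 10 or week 40.

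The gain is small and its rate is assumed: about 1 to 2 points of power at the planned loss. Nothing in the article shows that questionnaire length, rather than unopened e-mails, drives non-response. A short form offered late with an equal voucher could reward waiting and would cost ECI, CWS and MAKS data that the mediation analysis needs.

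These points limit the size of the finding but do not remove it. Saving partial answers does nothing for a carer who will not open a long assessment, and the reminder procedure as stated gives that carer no shorter choice.

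**Conclusion.** The point holds as an improvement to a stated procedure. The article fixes repeated e-mail links to one assessment as the retrieval route and describes no short route to its 14-item primary outcome, which is 12.5% of the counted full battery. It contains no error or contradiction on this point, and the sample size reproduces.

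The benefit is modest: at 20% loss, power moves from about 80.7% to 81.7–83.0% if 10–25% of non-completers respond, and by somewhat more if loss is heavier. This rests on the assumed recovery rate and a two-sample calculation that ignores the planned model's adjustments. The better reason for the change is that the added values would be observed outcomes from disengaged carers, for whom missing-at-random is weakest.

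**What to change.** In both arms, make the last one or two of the six 20-week reminders offer a WEMWBS-only form, within the same four-week window. Use those responses in the primary analysis, and record which form each carer completed. State also whether WEMWBS is presented first and whether partial answers are kept; if both are already so, a sentence is enough.

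The cost is a short form on the existing platform and new text in one or two automated e-mails. Recruitment is described as running in six cohorts, so the change could be made for cohorts yet to reach 20 weeks. The downside is that some late responders who would have completed everything will give WEMWBS only, leaving slightly fewer secondary and mediator data. Whether the short form earns the full voucher is for the sponsor to decide, since equal payment could encourage carers to wait for it.

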**Fig. 5 Fig5:**
[figure not shown]
Schedule of data collection. Detailed legend: T-1: Pre-randomisation; T0: baseline and randomisation; T1: mid-intervention; T2: end of intervention; T3: 40-week follow up; T4: after follow-up outcome data collection; WEMWBS: Warwick-Edinburgh Mental Wellbeing Scale; MAKS: Mental Health Knowledge Schedule; ECI: Experience of Caregiving Inventory; EQ-5D-5 L: EuroQol 5 level version of EQ-5D; FQ: Family Questionnaire; CWS: Carer Wellbeing & Support Questionnaire

### Sample size

The trial sample size is calculated with reference to an earlier study testing a digital health intervention targeting siblings of individuals with first episode psychosis [39] and the primary outcome measure data (i.e. WEMWBS [29]). This study is powered to detect the minimum clinically important difference of + 3 in WEMWBS which is considered a meaningful change post intervention between treatment groups [31]. Using 80% power, significance level of 5% and an estimated SD of 9 from the E Sibling Project RCT baseline results [13, 39], 143 carers per arm are needed. With estimated 20% attrition, additional participants (*n* = 74), will be recruited, leading to an overall sample size of 360 across both arms.

### Random allocation

Participants who have completed baseline measures before the respective cohort starts will be randomized using a 1:1 ratio to “COPe-support and usual care” versus “Control and usual care” by an online randomization programme developed and hosted by King’s Clinical Trials Unit. The algorithm for randomization will consist of permuted blocks stratified by the gender. While there is no established evidence of any carer sociodemographic or caregiving-related factors having an effect on carers’ health outcomes, females (having a caregiving role or not) are known to have worse outcomes in population mental wellbeing research [11, 12, 40] and that participants in most prior research recruiting carers were predominantly females.

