## Background

World-wide, an ever-increasing population is living longer in the community despite long-term illness. In addition to the advances of health care, one crucial element that support and sustain this population in their own home is the unpaid care and support provided by relatives and friends [1]. In the UK, it is estimated that approximately 1.5 million people are caring for a family member or friend with a mental illness [2–4]. Of these illnesses, psychosis is recognised as among the most common and severe [2, 3]. Often, people with psychosis require long-term treatment and support across a range of life domains, including emotional support, financial and practical assistance for daily living activities [5, 6]. Therefore, the importance of relatives and friends - referred to carers hereafter - is well established. Extant research evidence has established that individuals who receive support and care from their familial networks have a better prognosis and enhanced quality of life [3, 7, 8]. Conversely, the responsibility of caring often means that carers of people with psychosis experience high levels of distress and increased vulnerability to ill health [9–12]. Furthermore, carers’ psychiatric morbidities are shown to be inversely correlated with the amount of care they provide; that is, the higher amount of care provided leading to poorer mental health [13]. Poor mental health in carers can further negatively impact their caregiving capacity [9, 14]. Carers who are unwell themselves or feel they lack resources to cope are less likely to engage in caring for their loved ones in a positive manner [6].

Consequently, a body of research has been undertaken to establish psychosocial interventions which can best support carers [5, 6, 15]. Among these, psychoeducation (i.e. information-giving on the illness condition and related caregiving and problem-solving strategies) especially those integrated with a peer support element between carers in a group setting, has the strongest evidence base for its effectiveness in enhancing carers’ knowledge and coping with their caring roles [2, 16]. Carers also identify that sharing mutual support and learning with other carers as particularly useful in reducing their sense of isolation [5, 16]. In the UK, psychoeducation is recommended by the National Institute for Health and Care Excellence (NICE) guidelines on psychosis and schizophrenia for all carers [2].

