### Data analysis

#### Statistical analysis plan

The data analysis will be performed by the trial statisticians who will be blind to randomized allocation for the primary and secondary outcome analysis. Primary analyses will be undertaken on an intent-to treat (ITT) basis, including all participants who were randomized and supplied at least one post-randomisation measure at 10, 20, or 40 weeks, regardless of usage status or withdrawal from the study. For the primary analysis, a linear mixed model will be used. The model will include participant and cohort as random effects and arm, time (10, 20, 40 weeks), the randomization stratification variable gender as well as baseline score and a time-by-arm interaction. In order to improve precision we will adjust for variables parent (Y/N) and living with the cared-for individual (Y/N). The model’s assumptions for random effects distributions and residuals will be investigated. If assumptions are not appropriate then transformation will be considered. This model will be used to estimate the mean difference and 95% CI in WEMWBS between arms at the 20-week time point (i.e. primary endpoint) though we will also explore and report the intervention effect at week 10 and 40. The model will be fitted using restricted maximum likelihood (REML). Secondary outcome measures will be assessed using similar approach. No interim analyses will be performed.

It is unlikely that missing baseline data will be problematic for the analysis as baseline outcomes are required to be collected prior to randomization. Further, as the analysis uses a mixed model which is efficient for missing data under the missing at random assumption [41] no multiple imputation will be performed. Sensitivity analysis will include exploring the mean WEMWBS score at each time point if all participants with missing information was set at the highest and lowest values seen in the dataset.

Further analysis after the analyses of primary and secondary outcomes will not be blind as this is not feasible. The intervention effect in those that use COPe-support (defined as having at least two logins) will be estimated using a complier adjusted case analysis (CACE) with “usage” treated as both a binary and ordinal variable.

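### The stratification rationale denies any established caregiving predictor, against the Background and the primary model; collected caring time is left out of the model, at a small cost in precision

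*Protocol article*

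**What the plan says.** Four sections of the protocol article bear on this.

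- **Random allocation.** "The algorithm for randomization will consist of permuted blocks stratified by the gender". The reason given is that "there is no established evidence of any carer sociodemographic or caregiving-related factors having an effect on" carers' health outcomes, whereas women are known to have worse population wellbeing and make up most of earlier carer samples.
- **Background.** Carers' psychiatric morbidity is reported as related to the amount of care, explained as "the higher amount of care provided leading to poorer mental health".
- **Data collection.** Enrolment data include "how much time they spend on caring for their loved one in the previous week".
- **Statistical analysis plan.** The mixed model has participant and cohort as random effects, with arm, time, "the randomization stratification variable gender as well as baseline score and a time-by-arm interaction". For precision, "we will adjust for variables parent (Y/N) and living with the cared-for individual (Y/N". Caring time is not listed. Secondary outcomes are to be analysed in a similar way.

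**The concern.** Amount of care is a caregiving-related factor and mental health is a health outcome, so the Random allocation sentence and the Background sentence do not sit together. The analysis section adds a second conflict. Adjusting for parent status and co-residence improves precision only if those factors predict the outcome, so the model already assumes what the stratification rationale says is not established.

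The choice of covariates then looks uneven. The model takes two caregiving descriptors for which the article states no evidence. It omits the one that the article does link to poorer mental health, although that variable is already collected. Eligibility asks only for weekly contact in any form and sets no upper limit, so caring time may vary widely in the sample. At stake is the residual variance of the primary and secondary models, and hence the width of the confidence intervals.

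**Working it through.** **Text comparison.** The Random allocation section denies established evidence for any caregiving factor. The Background reports such evidence for amount of care. The analysis section treats parent status and co-residence as worth adjusting for. The first statement cannot stand unqualified beside the other two.

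**The plan's own sample size.** Inputs from the Sample size section: difference 3, SD 9, power 80%, significance level 5% (taken as two-sided).

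- n per arm = 2(1.960 + 0.842)² × 9² / 3² = 141.3, so 142. The t-test version gives 142.2, so 143, as stated.
- With 20% attrition: 143 / 0.8 = 178.75, so 179 per arm and 358 in total. The plan states 286 + 74 = 360, which agrees closely.
- Power at 143 per arm with SD 9 and no covariates is 80.5%.

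None of this depends on the disputed sentence.

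**What adding caring time is worth.** The documents give neither the correlation of baseline with 20-week WEMWBS (ρ) nor the share of the remaining variance that caring time would explain (partial R²). Both are assumed here: ρ from 0.5 to 0.7, and partial R² of 1% or 5%. Baseline WEMWBS is already in the model, so the partial R² must be applied to the baseline-adjusted SD and not to 9. Gender, parent status and co-residence are given no further credit.

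- SD without caring time: s₀ = 9√(1 − ρ²)
- SD with caring time: s₁ = s₀√(1 − R²)
- Power = Φ(3 / (s√(2/143)) − 1.960)

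| ρ | s₀ | Power without | Power, R² = 1% | Power, R² = 5% | Gain (points) |
|---|---|---|---|---|---|
| 0.5 | 7.79 | 90.2% | 90.5% | 91.6% | 0.3 to 1.4 |
| 0.6 | 7.20 | 94.1% | 94.3% | 95.1% | 0.2 to 1.0 |
| 0.7 | 6.43 | 97.7% | 97.8% | 98.2% | 0.1 to 0.5 |

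The gain therefore runs from about 0.1 to 1.4 points. In terms of the confidence interval, the standard error shrinks by the factor √(1 − R²), which is 0.995 at 1% and 0.975 at 5%. That is 0.5% to 2.5% narrower, whatever ρ is.

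**The same gain in carers.** With 360 × 0.8 = 288 analysed, the equivalent extra number is 288/(1 − R²) − 288, which is 2.9 at 1% and 15.2 at 5%.

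**The case against.** The case for leaving the model alone is a fair one.

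- **The wording is softer than a flat contradiction.** No established evidence of an effect is not the same as no effect, and the Background rests on one cited source. Its sentence is also muddled: "carers’ psychiatric morbidities are shown to be inversely correlated with the amount of care they provide" points the other way from the explanation that follows it. This stands in part. The explanation still makes the intended direction plain, and a finding described as shown does not fit with no established evidence.
- **A reader might infer that the protocol calls caring time prognostic for the primary outcome.** It does not. The Background speaks of psychiatric morbidity, whereas WEMWBS measures positive wellbeing. Nothing is said about prediction of the 20-week score once baseline is known, and baseline probably carries much of any such link. This stands in full.
- **A reader might infer bias or an underpowered trial.** Neither follows. Randomisation protects the comparison, chance imbalance is already reflected in the confidence interval, and the sample size reproduces without the disputed sentence.
- **A short pre-specified covariate list is legitimate, and co-residence may partly stand in for care intensity.** This is true, and the full analysis plan may explain the choice. But the article names its covariates, and its stated rationale still conflicts with them.
- **The added covariate is not quite free.** Caring time is taken at enrolment for a single week, and participants then wait for their cohort to start. Only baseline outcomes are said to be required before randomisation, and no multiple imputation is planned. If 1% of carers lacked the value and were dropped, about 3 of 288 would be lost, which cancels the gain at R² = 1%. This stands, and the fix has to deal with it.

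**Conclusion.** The point holds as a minor one. The sentence in Random allocation conflicts with the Background and with the protocol's own primary model, and a collected variable that the text links to poorer mental health is left out of that model without a stated reason.

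The consequence is a small loss of precision: about 0.1 to 1.4 points of power, or confidence intervals 0.5% to 2.5% wider than they need be. This rests on the assumed partial R² of 1 to 5% and, for the power figures, the assumed baseline correlation of 0.5 to 0.7. Applying the same partial R² to the raw SD of 9 would suggest a move from 80.5% to about 81 to 82%, but that starting point ignores the baseline score already in the model. A larger gain for the caregiving outcomes is conceivable, but the documents give nothing from which to size it. There is no case for changing the stratification.

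**What to change.** 1. Reword the sentence in Random allocation so that it agrees with the Background and the Statistical analysis plan section. For example, it could say that amount of care has been linked to carers' mental health, that gender was chosen as the only stratification factor, and that selected caregiving factors are handled by adjustment. The Background's description of the correlation as inverse should be corrected at the same time.
2. Before unblinding, add enrolment caring time as a fixed covariate beside parent status and co-residence, for the primary and secondary outcome models. Its form (continuous, transformed or categorical) should follow the item's response format, which the article does not give.
3. Pre-specify a simple fill-in for missing covariate values, so that no randomised carer leaves the analysis because of this term.

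The cost is one sentence and one model term, with no new data. The downside is a value that may be somewhat out of date by the start of the cohort, which would reduce the gain but not bias the comparison.
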